### Activity leader training and fidelity of intervention

All intervention sessions will be facilitated by activity leaders, who are professionally trained activity instructors or physical education teachers. A train-the-trainer approach will be adopted; all activity leaders will receive two half-day training workshops led by the lead author and a co-author before the start of the intervention. All training materials, including presentation slides and videos of the workshop, will be uploaded to an online resource platform accessible to activity leaders. The unit plan of intervention sessions, and materials to be used in intervention sessions will be provided via the platform. The training workshops will be videotaped and uploaded to the online resources platform shared to the activity leaders. The activity leaders can revisit the scenarios and critical ideas anytime anywhere they want.

The tenets of SDT [31] and SAAFE teaching principles [45] will be introduced to activity leaders during training workshops. The activity leaders will be trained to apply the theory and teaching principles in all of the activity sessions. More specifically, the activity leaders will be trained to deliver sessions that are: (i) Supportive (i.e. the activity leaders should be supportive and exert their endeavors to promote positive interactions between parents and their children), (ii) Active (i.e. sessions should be highly active and with minimal transition time), (iii) Autonomous (i.e. sessions should involve opportunities for participants’ choice), (iv) Fair (i.e. all participants should be provided with opportunities to experience success), and (v) Enjoyable (i.e. sessions should be enjoyable with a variety of activities). As such, a practical session would be provided during the training. Ample time and opportunities will be given to the activity leaders to implement the aforementioned teaching techniques for different activities. There will be a follow-up small group discussion session immediately after the practical session, and the activity leaders can also ask questions and receive feedback from the lead author and a co-author. Further, activity leaders will be provided with a self-reflective questionnaire based on the SAAFE principles to complete after each intervention session. This process will help activity leaders to identify things they have done well and areas for improvement.

A half-day top-up training workshop will be provided to the activity leaders at the mid-point of the intervention to collectively reflect on their teaching experiences. This will provide them with an opportunity to share their barriers to implementation and potential solutions. To ensure the intervention delivered by each activity leader is comparable, all intervention sessions will be video-recorded and at least two sessions be reviewed and assessed with reference to a “SAAFE Principles Observation Checklist” (e.g., “Provide private rather than public feedback”, “involve participants in the creation and modification of activities and rules”). Activity leaders can also view the video-recorded sessions of their counterparts online, and they are encouraged to share their teaching experiences, discuss and comment on each other’s teaching to create a more mutually supportive environment among activity leaders.

### Primary and secondary outcomes of the trial

The primary outcome of the randomized controlled trial is children’s MVPA. Parents’ MVPA and the time parents and children spend doing activity together (co-physical activity) will be measured as secondary outcomes. Other secondary outcomes of the trial include (i) parents’ and children’s FMS competency, (ii) parents’ and children’s BMI, (iii) children’s perceived need support and control, (iv) parents’ provision of need support and psychological control, (v) children’s and parent’s basic psychological needs satisfaction and thwarting, (vi) parents’ motivation towards physical activity, (vii) children’s and parent’s well-being.

#### Moderate-to-vigorous physical activity – Children and parents

Children’s and parents’ time spent in daily MVPA over a five-day period will be measured using ActiGraph wGT3X-BT accelerometers worn at the waist. Using the criteria developed by Evenson, Catellier, Gill, Ondrak and McMurray [46] (for children) and Freedson, Melanson, and Sirard Freedson, Melanson, and Sirard [47] (for parents), the sum of daily minutes spent in moderate and vigorous activity will be used as a measure for MVPA. One-second epochs will be used for the calculation of MVPA [48]. Cases will be considered valid if participants wore the accelerometer for at least eight hours on a minimum of three days, with at least one weekend day. Using proximity sensors in the ActiGraph devices [49], the duration of co-physical activity periods per day will also be measured. Participants will be required to wear the devices throughout their waking hours within the five-day data collection period except during any water-based activities (e.g., water sports, bathing) or occasion where they are not allowed to wear the devices (e.g., a contact sports match).

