**Methods:**

“Active 1 + FUN” is a family-based intervention designed using the tenets of self-determination theory. The intervention was designed to help parents support their children’s basic psychological needs for competence (by providing informational feedback and optimal challenges), autonomy (by exploring a variety of activities and reducing controlling behaviors), and relatedness (by increasing co-PA between parents and child). The intervention components include interactive workshops, activity sessions, physical activity homework, activity planning consultations, easy sports equipment, and online materials. A randomized controlled trial will be conducted to evaluate the intervention. A target sample of 204 Primary three to five students (8 to 11 years) and their parents will be randomly allocated to the experimental group or a wait-list control group. The experimental group will receive a ten-session intervention which spans approximately six months. The control group will receive intervention one year later. Children’s accelerometer-based leisure-time physical activity (primary outcome) and secondary outcomes will be assessed at baseline, at end of intervention period (6 months after baseline), and at follow-up (12 months after baseline). Qualitative interviews will be conducted to determine effective intervention components from the perspective of children and parents. We hypothesize that the intervention will increase parents’ and children’s activity behaviors and that children will experience higher levels of needs satisfaction with regard to physical activity participation.

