The effectiveness of the intervention will be evaluated using a randomized controlled trial. Eligible children and their parents will be randomly assigned to the experimental group or a wait-list control group. Quantitative measures will be taken at baseline, at the end of intervention period (accelerometer measure will be taken during a period that included the day of the tenth intervention session, secondary outcomes will be taken the week immediately before the session) and post-intervention follow-up (one year after baseline), for all children and their parents who took part in the intervention. The primary outcome of the trial will be time children’s spent in leisure-time MVPA, measured objectively using accelerometers.

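### The wear rule secures weekend hours but no after-school hours on weekdays, and an unadjusted sum of daily minutes lets a post-baseline wear difference pass into the leisure-time MVPA effect

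*Protocol article*

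**What the plan says.** The Protocol article describes the primary outcome in two ways. The last paragraph of the Background says: "The primary outcome of the trial will be time children’s spent in leisure-time MVPA, measured objectively using accelerometers". The abstract also calls it leisure-time activity. The section on primary and secondary outcomes drops the restriction: "The primary outcome of the randomized controlled trial is children’s MVPA".

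The measurement section (Moderate-to-vigorous physical activity – Children and parents) concerns daily MVPA over five days. It fixes three things:

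- **Scoring:** "the sum of daily minutes spent in moderate and vigorous activity will be used as a measure for MVPA".
- **Validity:** "Cases will be considered valid if participants wore the accelerometer for at least eight hours on a minimum of three days". With the end of that sentence, the full condition is wear of "at least eight hours on a minimum of three days, with at least one weekend day".
- **Wear instruction:** "Participants will be required to wear the devices throughout their waking hours within the five-day data collection period", with exceptions for water-based activities and for occasions where the device is not allowed.

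It gives no rule for separating leisure time from the rest of the day, and it does not say where in the day the eight hours must fall. The main model under Statistical methods contains time, group and their interaction. Covariates are unnamed and enter additional analyses only.

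**The concern.** The programme is meant to act after school and at weekends; the Background (Inactivity in children: The Hong Kong context) identifies these as the periods that school-based interventions leave uncovered. The validity rule protects the weekend part of that window. It does not protect the weekday part, because eight hours of wear can be largely or wholly used up by the school day.

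A sum of minutes can count only what was recorded. Unless it is adjusted, after-school hours not worn add nothing to it, so the score depends on compliance as well as activity. With equal compliance in both arms this adds noise. If wear comes to differ between arms after baseline, the difference goes into the time-by-group coefficient, which is the plan's test of effect.

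Such a difference is possible here, though not shown. Participants are not blinded. During the trial year only the experimental arm receives MVPA results, feedback and activity planning (Table 1). The second accelerometer period includes the day of the tenth session.

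**Working it through.** **1. The plan's own sample size.** Inputs from Sample size calculation: d = 0.5, Type I error 0.05 (taken as two-sided), power 0.80, 30% non-compliance, 10% drop-out. The two-sample t-test gives 63.77, so 64 per arm and 128 in total. Inflation: 128 / (0.70 × 0.90) = 203.2, so 204. Both stated figures reproduce, and this point does not change them.

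**2. What the smallest valid record contains.** From the validity rule: 3 days × 8 h = 24 h of wear, of which at least 8 h (8/24 = 33%) fall on a weekend day.

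Assumptions, not in the document: school day S = 6 to 8 h; waking day W = 13 to 15 h; all weekend hours are leisure; the other two days are school days, with wear starting when school starts.

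- Leisure observed per school day = 8 − S, that is 0 to 2 h.
- Leisure observed over three days = 8 + 2 × (8 − S).
- Leisure available over three days = W + 2 × (W − S).

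| S (h) | W (h) | Observed (h) | Available (h) | Share of available | Share on each school day |
|---|---|---|---|---|---|
| 6 | 13 | 12 | 27 | 44% | 2/7 = 29% |
| 7 | 14 | 10 | 28 | 36% | 1/7 = 14% |
| 8 | 15 | 8 | 29 | 28% | 0/7 = 0% |

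So the smallest valid case shows 28% to 44% of the leisure time on its three days, and 0% to 29% on each school day.

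**3. What a wear difference would do.** Assumptions, not in the document: 3 to 5 MVPA minutes per worn hour, and an SD of 20 minutes per day. Bias = wear difference × rate; d = bias / 20.

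| Post-baseline wear difference | Bias (min/day) | d |
|---|---|---|
| 0 h | 0 | 0 |
| 0.5 h | 1.5 to 2.5 | 0.075 to 0.125 |
| 1 h | 3 to 5 | 0.15 to 0.25 |

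Against the planned d = 0.5, the one-hour row is 0.15/0.5 = 30% to 0.25/0.5 = 50%. With 64 per arm and no true effect, a two-sample t-test would reject in about 13% (d = 0.15), 20% (d = 0.20) or 29% (d = 0.25) of trials, against a nominal 5%. This is a single-visit comparison at 6 months. Under the planned model it applies only to a difference that emerges after baseline; a stable difference cancels from the interaction.

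**The case against.** A reader might infer that a child who wears the monitor only at school would count as valid with almost no leisure time observed. The document rules this out: without a valid weekend day the case is excluded, so every valid case has at least 8 weekend hours. The Background also notes that families spend much of their time together at weekends, so the rule secures an important part of the target window. That part of the defence stands in full.

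A reader might likewise take a day at the eight-hour floor, with 6 of 14 assumed waking hours (43%) unrecorded, as typical. It describes one day at the minimum. Participants are told to wear the device for all waking hours, and nothing in the document shows that weekday wear clusters at the floor.

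Nor does the document show that the experimental arm will wear the device longer. The HK$100 voucher per completed assessment is the same in both arms. The one-hour gap, the MVPA rate and the SD are all assumed.

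Finally, non-wear handling and wear adjustment could sit in a fuller protocol or analysis plan that is not shown, so their absence alone is weak evidence. What remains is the rule that is written down: it does not require weekday wear in the period that the outcome names. A later adjustment can account for unequal wear, but it cannot recover hours that were never recorded.

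**Conclusion.** The concern holds for weekdays, not for the whole case. Leisure-time MVPA is named as primary, yet the stated rule accepts weekdays with no after-school wear, the score is a sum of daily minutes, and the main model has no wear term. Up to two of the three days in a minimum valid case can therefore say little about the outcome; the 28% to 44% share rests on the assumed lengths of the school and waking day.

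The possible bias is conditional. It needs a between-arm change in wear after baseline, which is plausible but undocumented. The d of 0.15 to 0.25 for one hour illustrates sensitivity and does not predict bias in this trial. The stated sample size is unaffected unless the validity rule is tightened.

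**What to change.** 1. Define the leisure window: after school on weekdays, all waking hours at weekends. Score the primary MVPA outcome within it and use one outcome definition in every section.
2. Adjust the primary model for wear time in that window, or express MVPA per worn leisure hour.
3. Report leisure wear time by arm and visit.
4. Keep the rule of eight hours on three days with a weekend day, and add a minimum after-school wear on weekdays, either in the primary definition or as a sensitivity definition. Fix the cut-off before the data are seen.

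Steps 1 to 3 are processing and analysis changes that use time-stamped records and need no new data collection. Standardising or adjusting assumes that unworn leisure time resembles worn leisure time.

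Step 4 may push non-compliance above the assumed 30%. By the plan's own formula, 35% would need 128 / (0.65 × 0.90) = 218.8, so 219 children, and 40% would need 128 / (0.60 × 0.90) = 237.04, so 238, against 204. If that is not affordable, use the stricter rule as a sensitivity definition, which leaves the target at 204.

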#### Fundamental movement skills competency – Children and parents

Four FMS of children and parents will be assessed, namely, kick, catch, overhand throw, one-hand forehand strike. These skills will be assessed using the Test of Gross Motor Development-3 (TGMD-3) [50]. Using the protocol by Chan et al. [51], participants will first be shown a video demonstration of the skill to be assessed. Their performances with then be video-taped and assessed using the TGMD-3. The videos will be reviewed and rated by a trained research assistant with a degree in physical education.

#### Body mass index – Children and parents

Participants’ body height and weight will be measured to calculate their BMI. This outcome will be used as a pseudo-measure of their physical health.

#### Children’s perceived need support and control – Children only

The degree to which children perceive their parents to be need-supportive or controlling will be measured using an adapted version of Perceived Parental Autonomy Support Scale [52]. The adapted scale comprises of six items measuring need supportiveness (e.g., “Within certain limits, my parents allowed me the freedom to choose my own activities”) and seven items tapping psychological control (e.g., “When my parents wanted me to do something differently, they made me feel guilty”). Respondents will provide responses using a 7-point scale from 1 (“Do not agree at all”) to 7 (“Very strongly agree”).

#### Provision of need support and psychological control – Parents only

Parents will be asked to self-report the *frequency* in which they use need supportive or controlling strategies in relation to their children’s physical activity behaviors. Items will be adapted from the scale used to measure children’s perceived support. Example items include: “Within certain limits, I allowed my child the freedom to choose their own activities”, “When I asked my child to do something differently but he/she does not listen, I will make him/her feel guilty”. Responses will be made using a 5-point scale ranging from 1 (“Never”) to 5 (“Always”).

#### Basic psychological needs satisfaction and frustration – Children and parents

The satisfaction and frustration of three basic psychological needs of autonomy, competence, and relatedness have essential consequences for one’s physical and psychological health [33]. Children and parents’ perceived basic need satisfaction and frustration will be measured using a scale adapted from Ng, Ntoumanis, Thøgersen-Ntoumani, Stott, and Hindle [53]. The 18-item scale measures the facets of perceived basic need satisfaction or furstration towards physical activity participation; for instance, “People I know tell me I am good at sports” (competence satisfaction), “I feel free to choose what to do” (autonomy satisfaction), “people around me care for me” (relatedness satisfaction), “I encountered situations where I was made to be incompetent” (competence frustration), “I feel forced to follow decisions made for me” (autonomy frustration), and “I feel others dislike me” (relatedness frustration). Respondents will make responses using a 7-point scale from 1 (“Strongly disagree”) to 7 (“Strongly agree”).

#### Well-being – Children and parents

The Cantonese versions of the KIDSCREEN health-related quality of life questionnaire [54] will be used as a measure for children’s well-being. It is a ten-item questionnaire which assesses children’s physical well-being (e.g., “Have you felt fit and well?”), psychological well-being (e.g., “Have you felt sad?”), autonomy (e.g., “Have you been able to do the things that you want to do in your free time?”) and parent relation (e.g., “Have your parent[s] treated you fairly?”), peers and social support (e.g., “Have you had fun with your friends?”, and school environment (e.g., “Have you got on well at school?”). Respondents will make responses using a 5-point scale from 1 (“Never”) to 5 (“Always”). A Chinese version of the Flourishing Scale [55] will be used to measure parents’ psychological well-being. The scale consists of eight items which measure the facets of one’s psychological well-being; for instance, the positive relationships and having life meaning and purpose (e.g., “I am engaged and interested in my daily activities”). Respondents will respond using a 7-point scale from 1 (“Strongly disagree”) to 7 (“Strongly agree”).

### Blinding

Participants and activity leaders will not be blinded to group allocation, since only those allocated to the experimental group will attend the intervention sessions in the first year. Research assistants who are responsible for data collection will be blinded to group allocation at all time points.

### Statistical methods

Data analyses will be conducted using linear mixed models using an intention-to-treat approach. Group differences concerning all primary and secondary outcomes will be examined. Specifically, a two-level (i.e., level 1 = time, level 2 = individual) model will be examined for each outcome, using the equation: Outcome = B_0_ + B_1_*Time + B_2_*Group + B_3_*Time*Group. The B_1_ coefficient will be parameterized as a variable with random slope and random intercept at all levels. Additional analyses will be conducted by adding the potential covariates and mediators to the models. An intervention effect will be deemed to be present if the B_3_ coefficient was statistically significant from zero.

Structural equation modelling will also be used to test the structural model of children’s perceived need support/control predicting need satisfaction/thwarting, and in turn physical activity behaviors and well-being. In the same model, we will examine the relationship between parents’ self-reported need supportive/controlling behaviors and children’s perception of the same constructs. Based on the work of Radel, Sarrazin, Legrain, and Wild [56], we will also examine the link between parents’ need satisfaction and their parenting styles in the model. To account for the relatively small sample size, a Bayesian approach will be used for structural equation modelling analyses (e.g., [53]).

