**Fig. 1 Fig1:**
[figure not shown]
Flow diagram of the cluster randomized controlled trial

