### Sample size calculation

A power calculation was conducted to estimate the required sample size. Power calculation was based on the primary outcome of children’s MVPA, at the primary time point of 6-months. Calculations were conducted using G*Power 3.1.7. Based on the Healthy Dads, Healthy Kids study [29], intervention effect size was estimated at *d* = 0.5. With a Type I error probability of 0.05 and power of 0.8, the required sample size was calculated to be *N* = 128. To account for an estimated accelerometer non-compliance rate of 30% (i.e., cases with insufficient wear time) and a potential drop-out rate of 10% [14], a minimum of *N* = 204 children will be recruited.

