### Procedures and randomization

Measures for primary and secondary outcomes will be taken at baseline, at the end of intervention period (accelerometer measure will be taken during a period that included the day of the tenth intervention session, secondary outcomes will be taken the week immediately before the session), and post-intervention follow-up (i.e., one year after the baseline measurement) to examine long-term intervention effects. After completing baseline measures, participants will draw a sealed envelope to determine whether they will be allocated to the experimental group or the wait-list control group. In each school, half of the recruited families will be allocated to the experimental group, and the other half will be allocated in the wait-list control group (i.e., 1:1 ratio). Participants allocated to the experimental group will receive ten bi-weekly intervention sessions over approximately 6 months immediately after baseline measures are taken. Participants allocated to the control group will be asked to attend measurement sessions, but they will only receive the intervention 12 months later (i.e., after the final follow-up time point). Each family will receive a HK$100 gift voucher for each completed assessment for the child and at least one parent. Intervention sessions will take place within school premises. All intervention sessions for a particular class will be led by the same activity leaders (two per session) throughout the intervention period. To encourage participation, each family will receive a transportation subsidy of HK$40 for the interactive workshops and activity sessions that they attend.

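### Only the experimental arm is treated in fixed classes, but the primary model and the N = 128 calculation treat children as independent; any within-class correlation makes the B3 standard error too small and power lower than 80%

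*Protocol article*

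**What the plan says.** Under Statistical methods, "a two-level (i.e., level 1 = time, level 2 = individual) model will be examined for each outcome". The equation contains Time, Group and their product. Random effects are placed at all levels, and only those two levels are defined. An effect is declared when B3 differs significantly from zero. Covariates and mediators enter only in additional analyses.

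Under Procedures and randomization, "In each school, half of the recruited families will be allocated to the experimental group", so families are allocated 1:1 inside each school. The same section says: "All intervention sessions for a particular class will be led by the same activity leaders (two per session) throughout the intervention period". Controls receive the intervention only after the 12-month follow-up.

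Under Sample size calculation, "intervention effect size was estimated at *d* = 0.5". Then, "With a Type I error probability of 0.05 and power of 0.8", "the required sample size was calculated to be *N* = 128". No ICC, class size or design effect is mentioned. The target of 204 allows for 30% accelerometer non-compliance and 10% drop-out.

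The Fig. 1 caption reads "Flow diagram of the cluster randomized controlled trial", which does not match the allocation described in the text.

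**The concern.** This is a partially nested design: children in one arm share a class, two leaders and a school's delivery conditions, and children in the other arm share none of these. The protocol itself gives reasons to expect some class effect:

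- Sessions are video-recorded and a sample is reviewed so that delivery is comparable across leaders (Activity leader training and fidelity of intervention).
- The length of the intervention may differ between schools (Intervention).
- The end-of-intervention accelerometer window includes the day of the tenth session (Procedures and randomization), so a shared class activity can fall inside the primary measurement.

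A shared deviation that appears after baseline in one arm is not absorbed by individual random intercepts and slopes. It falls directly on the contrast that B3 estimates. At stake are the 5% error rate of the rule for declaring an effect and the stated 80% power.

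**Working it through.** **Inputs from the protocol.** d = 0.5, alpha 0.05, power 0.80, N = 128, losses of 30% and 10%, target 204, eight schools, 1:1 allocation within school.

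**Assumptions, because the protocol gives no value.** One experimental class per school and a class ICC of 0.01 to 0.10. Evaluable children: 204 × 0.70 × 0.90 = 128.5. Over 8 schools and 2 arms this is 128.5/16 = 8.03, so m = 8 per class.

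**Reproducing the plan's figures.** A two-sided two-sample t-test with 64 per arm has power 0.801 (63 per arm gives 0.795), so N = 128. Then 128/(0.70 × 0.90) = 203.2, rounded up to 204. Both figures are correct for independent children.

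**Class effect in the experimental arm only.**

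- Design effect in that arm: DE = 1 + (m − 1) × ICC = 1 + 7 × ICC.
- Variance ratio for the group difference: V = (DE + 1)/2.
- Type I error of the unadjusted test: 2 × [1 − Φ(1.96/√V)].
- Power of a test with the correct standard error, normal approximation: Φ(0.5/√(2V/64) − 1.96).
- Satterthwaite df: (DE + 1)² / (DE²/7 + 1/63), with power from the noncentral t.

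Worked line at ICC 0.05: DE = 1.35 and V = 1.175. Then 1.96/√1.175 = 1.808, so type I error is 7.1%. The noncentrality is 2.828/√1.175 = 2.609, so power is Φ(0.649) = 74.2%.

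| Class ICC | DE | V | Type I, unadjusted | Power, normal | Power, df 126 | Satterthwaite df | Power, Satterthwaite |
|---|---|---|---|---|---|---|---|
| 0 | 1.00 | 1.000 | 5.0% | 80.7% | 80.1% | 25 | 77.6% |
| 0.01 | 1.07 | 1.035 | 5.4% | 79.4% | 78.8% | 24 | 76% |
| 0.02 | 1.14 | 1.070 | 5.8% | 78.1% | 77.4% | 23 | 74% |
| 0.05 | 1.35 | 1.175 | 7.1% | 74.2% | 73.5% | 20 | 70% |
| 0.10 | 1.70 | 1.350 | 9.2% | 68.2% | 67.6% | 17 | 63% |

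A simulation of change scores (20,000 replicates, 8 schools, 8 + 8 evaluable children each, unadjusted t-test) gave type I error of 5.6%, 7.2% and 9.1% at class ICC 0.02, 0.05 and 0.10.

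**School effect common to both arms.** With balance inside schools the variance factor is 1 − ICC. For a school ICC of 0.02, 0.05 and 0.10 in the change, the unadjusted type I error is 4.8%, 4.4% and 3.9%, and power is 81.0%, 81.4% and 82.0%. When schools differed only in level and not in change, the simulated type I error was 5.0%.

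**Both together at 0.05.** V = (0.95 + 0.95 + 7 × 0.05)/2 = 1.125. Type I error is 6.5% (6.2% by simulation) and power is 76% before any df correction.

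**The case against.** A reader might infer that allocation within schools itself spoils the standard errors. It does not. School effects are balanced across arms, stable ones drop out of B3 through the individual intercept, and the remainder makes the unadjusted test slightly conservative. This also partly offsets the class inflation, as the combined case shows.

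A reader might also conclude flatly that the standard errors and the 80% are wrong. The documents do not establish that. They give no ICC and no class size; at ICC 0.01 the loss is about one point of power, and the effect becomes material at about 0.05. Part of the Satterthwaite loss is not clustering at all: moving from df 126 to df 25 at ICC 0 already costs 80.1 − 77.6 = 2.5 points.

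The power formula is for a comparison at one time point, whereas B3 is a change contrast. Its variance factor is 2(1 − r) for a baseline-to-follow-up correlation r that is not given: 1.2 at r = 0.4 and 0.8 at r = 0.6. Absolute power could therefore be worse or better than tabulated. This objection stands. It does not remove the relative inflation from a class effect on the change, nor the resulting type I error.

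Finally, the caption might be read as showing that schools were randomized, which would call for a whole-school design effect. The Abstract, the Background and Procedures and randomization all describe random assignment of children with their parents, the last by envelope with half the families in each school. One word in a caption does not outweigh that.

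**Conclusion.** The point holds conditionally. The stated primary test and the sample size omit the one source of clustering that can bias B3's standard error downwards: delivery classes in the experimental arm. The model's levels and the decision rule are fixed in the text, so this is not detail left to an analysis plan.

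Under the assumed 8 classes of 8, a class ICC of 0.01 to 0.10 gives type I error of about 5.4% to 9.2% and power of about 79% to 68% before a small-sample correction, or 76% to 63% with one. These ranges rest on the assumed ICC and class size and on an outcome variance equal to that implied by d = 0.5. The arithmetic behind 128 and 204 is sound for independent children. The Fig. 1 caption contradicts the text regardless of any assumption.

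**What to change.** - In the primary model, add school as the allocation block and include school-by-time. A school main effect alone would barely change B3.
- Add a random class effect on the post-baseline contrast in the experimental arm only, with Satterthwaite or Kenward-Roger degrees of freedom.
- State the number and size of classes, and restate the power of the planned 204 children over a stated range of class ICC and class size. Compute it under the exact model adopted: with one class per school and fixed school-by-time terms, B3 rests on eight within-school differences, and the degrees of freedom can approach 8 − 1 = 7, fewer than in the table.
- Change the Fig. 1 caption to describe families randomized within schools.

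The cost is some rewording, somewhat wider intervals and a less favourable stated power. No added recruitment is needed.
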